**Abstract**

Vascular calcification (VC) is an active process, resulting from the disturbance of balance between inhibitors and promoters of calcification, in favor of the latter. Matrix Gla Protein, a powerful inhibitor of VC, needs vitamin K to become active. In vitamin K depletion, plasma levels of the inactive form of MGP, dephosphorylated, uncarboxylated MGP (dp-ucMGP) are increased and associated with VC and cardiovascular (CV) outcomes. End Stage Renal Disease (ESRD) patients have increased circulating dp-ucMGP levels and accelerated VC. VItamin K In PEritoneal DIAlysis (VIKIPEDIA) is a prospective, randomized, placebo-controlled trial, evaluating the effect of vitamin K2 supplementation on arterial stiffness and CV events in ESRD patients undergoing peritoneal dialysis (PD). One hundred and twenty PD patients will be included in the study. At baseline, dp-ucMGP and pulse-wave velocity (PWV) will be assessed and then patients will be randomized (1:1 ratio) to vitamin K (1000 μg MK-7/day) or placebo for 1.5 years. The primary endpoint of this trial is the change in PWV in the placebo group as compared to the treatment group and the occurrence of CV events. Secondary endpoints are mortality, changes in PD adequacy, change in 24-hour ambulatory blood pressure indexes and aortic systolic blood pressure and changes in calcium/phosphorus/parathormone metabolism.

VIKIPEDIA is a new trial aiming to determine the effect of vitamin K2 supplementation on VC, CV disease and calcium/phosphorus metabolism, in PD patients. The protocol of this study is registered at ClinicalTrials.gov with identification number NCT04900610.

1. **Introduction**

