In the light of the growing body of data supporting the tight association between vitamin K deficiency and VC in uremia, several investigators are currently conducting randomized clinical trials examining the possible therapeutic effect of MK-7 supplementation on VC in ESKD patients (17) undergoing maintenance HD (BASIK2, VitaVasK, VitaK-CAC, Trevasc-HDK and Aortic Valve DECalcification trials). In *clinicaltrials.gov* the search terms “vitamin K” and “hemodialysis” produces 20 results of ongoing or completed RCTs (assessed 23/02/2021). However, none of these trials have been conducted in PD patients, but only in pre-dialysis CKD and/or HD subjects. Moreover, the majority of these trials assessed surrogate VC markers and not clinical hard end-points such as mortality and CV events and no study so far has evaluated the potential effect of MK-7 intake on 24-h ambulatory blood pressure (BP). Another issue of on-going RCTs in HD patients is that the daily dosage of MK-7 is usually below 500 μg/day (18). The precise required MK-7 dosage to restore vitamin K depletion and thus fully activate MGP in ESKD patients is not yet determined. However, in a dose-finding study in prevalent HD patients, Caluwe et al., showed that a daily dosage of 463 μg MK-7 caused a moderate 46% decrease in dp-ucMGP levels and therefore, it was considered under-therapeutic (19). Moreover, supplementation of MK-7 dosages<463 μg/day in HD patients failed to show any beneficial effect on VC in a recent RCT (20). Under these results, in another ongoing RCT in HD patients the proposed dosage of MK-7 is much higher -2 g thrice weekly (trial number *NCT04539418).* The proposed Vitamin K In PEritonial DIAlysis (VIKIPEDIA) study will assess whether high (1g/day) per os intake of MK-7 can enhance MGP activation, suppress dp-ucMGP and thus improve arterial stiffness and ameliorate CV disease.

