Oral administration of vitamin K2 might improve MGP carboxylation and phosphorylation status and thus decrease circulating dp-ucMGP. Vitamin K2 (Menaquinone-7, MK-7) is the first and most clinically approved and validated K2 supplement (MenaQ7 ®, Nattopharma, ASA, Hovik, Norway) with proven efficacy in reducing dp-ucMGP (21) and has been used in several clinical trials in HD patients (19, 22). Vitamin K2 is a natural supplement, that can be purchased over the counter from drug stores or even super markets, without physician’s prescription, because it is not a drug. Millions of people around the world are receiving vitamin K2, because it is thought to have several beneficial effects, whereas not toxicity or side effects have been reported. In the VIKIPEDIA study we will administer orally, daily, high dosage of MK-7 to PD patients. Although several clinical trials have administered MK-7 in dosages 200-500 μg/day, this is the first RCT administering 1g/day in PD patients. There are no safety concerns with this dosage, because other RCTs have administered MK-7 in ESKD, without reporting thrombotic events, side-effects or complaints (22).

Therefore, since ESKD patients undergoing PD present significant reduced K2 levels compared to pre-dialysis CKD patients, we believe that such a high dose is justified in our cohort and the potential beneficial effects of high-dose treatment might outweigh the potential side-effects. Finally, so far, no study has assessed the pharmacokinetics and pharmacodynamics of dp-ucMGP in PD patients and the concentration of dp-ucMGP in the PD effluent, after a PD session. Therefore, the proposed VIKIPEDIA study is novel and timely.

1. **Objectives**

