VIKIPEDIA is a multi-centre, placebo-controlled, randomized, open-label intervention clinical trial on PD patients. Our study protocol was developed in accordance with the Helsinki Declaration of Human Rights and the Good Clinical Practice Guidelines and Standard Protocol Items: Recommendations for Intervention Trials (23), was approved by the Ethics Committee/Scientific Council of the Medical School of Aristotle University of Thessaloniki (235/14.05.2021). All participants will provide a structured, written, informed consent. Three university, tertiary hospitals in Northern Greece with major, referral PD units will participate in the study. The design of the trial is presented in figure 1. In short, the patients will be recruited within 1 year. At baseline, all eligible patients who have provided a written, informed consent will be enrolled in the study. Αortic stiffness and vitamin K status will be assessed by PWV and plasma dp-ucMGP levels respectively. Before randomization, we will draw blood (serum and plasma) and PD fluid samples from all patients to measure blood count and routine biochemical parameters, including urea, creatinine, potassium, sodium, calcium, phosphorus, c-reactive protein, alkaline phosphatase, albumin, parathormone, 25-OH D3, magnesium, glycated hemoglobin, thyroid function hormones. Since both vitamin D and magnesium are considered of utmost importance in vitamin K metabolism, after baseline, patients with vitamin D and/or magnesium depletion will be treated with oral supplements to achieve normal levels of both elements, before randomization. Our cohort will then be categorized to one of the two groups (placebo or active group) and the treatment period will last 1.5 years. As mentioned before, vitamin K2 is a natural supplement, that can be purchased over the counter and it is not a drug.

To ensure that the two parallel groups will include patients that will not differ significantly in vitamin K and stiffness we will stratify the patients accordingly. However, since the clinicians that will assess PWV, 24hour BP and the study endpoints will be blinded to the treatment, information bias is excluded. After randomization, all patients will continue their routine, standard medical treatment and patients in the treatment group will additionally receive daily, per os 1 g of vitamin K2 (MenaQ7 ®, Nattopharma, ASA, Hovik, Norway).

*Inclusion and exclusion criteria*

Inclusion and exclusion criteria of this study are shown in Table 1.

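### The daily MK-7 dose is 1000 μg in the Abstract but 1 g in the Introduction and Methods, a 1000-fold contradiction in the definition of the intervention

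*Protocol*

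**What the plan says.** The study dose appears in four places.

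- **Abstract:** patients are "randomized (1:1 ratio) to vitamin K (1000 μg MK-7/day) or placebo for 1.5 years".
- **Introduction, dose rationale:** the study "will assess whether high (1g/day) per os intake of MK-7 can enhance MGP activation".
- **Introduction, safety paragraph:** "this is the first RCT administering 1g/day in PD patients".
- **Materials and Methods, Trial Design and Setting:** "patients in the treatment group will additionally receive daily, per os 1 g of vitamin K2". This is the only sentence in the Methods that states the dose.

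Two further statements in the Introduction lean on the dose. Directly after the second 1 g/day figure comes "There are no safety concerns with this dosage, because other RCTs have administered MK-7 in ESKD". The next paragraph adds "we believe that such a high dose is justified in our cohort".

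Table 1, the sample size section and the Monitoring section state no dose. No capsule strength or daily number of capsules is given anywhere in the readable text.

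**The concern.** The dose is the intervention. A reader who works from the Abstract and one who works from the Methods would describe two different trials. The Methods paragraph is the natural source for dispensing, and it carries the figure that disagrees with the Abstract.

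Several things hang on the answer. The compliance check in the Monitoring section counts remaining pills, which needs a defined daily quantity. Adverse events, and any effect on pulse wave velocity or cardiovascular events, can be interpreted only at a known exposure. The consent risk statement and the ethics approval must describe the dose actually given. The safety assurance also refers to the dosage just stated, so its meaning changes with the figure.

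**Working it through.** **1. Convert to one unit.** 1 g = 1,000,000 μg.

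| Place | As stated | In μg/day |
| --- | --- | --- |
| Abstract | 1000 μg/day | 1,000 |
| Introduction, dose rationale | 1 g/day | 1,000,000 |
| Introduction, safety paragraph | 1 g/day | 1,000,000 |
| Methods, Trial Design and Setting | 1 g daily | 1,000,000 |

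Ratio: 1,000,000 / 1,000 = 1000. The count is one place against three. The microgram symbol is intact in the Abstract and throughout the Introduction, close to the gram figures, so faulty text extraction is an unlikely explanation.

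**2. Compare with the protocol's own reference doses.** The Introduction describes 463 μg/day as insufficient in a dose-finding study in haemodialysis, and gives 200–500 μg/day as the range in several clinical trials.

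| Reference dose | 1000 μg/day is | 1 g/day is |
| --- | --- | --- |
| 463 μg/day | 1,000/463 = 2.16-fold | 1,000,000/463 ≈ 2,160-fold |
| 500 μg/day | 2-fold | 2,000-fold |
| 200 μg/day | 5-fold | 5,000-fold |

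**3. Total exposure.** Over 1.5 years, 1.5 × 365 = 547.5 days. The total is 547.5 × 0.001 g ≈ 0.55 g under the Abstract and 547.5 × 1 g = 547.5 g under the Methods.

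**4. The gram-range comparator.** The Introduction also cites another ongoing haemodialysis trial with a proposed 2 g three times a week. That is 6 g per week, or 6/7 ≈ 0.86 g/day. Per week it is close to this study's 7 g at 1 g/day, and about 857 times the 7,000 μg at 1000 μg/day (6,000,000/7,000). This figure is in grams too and cannot be checked from the document.

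**5. The safety statement.** It follows immediately on the 1 g/day figure, so that is the dosage it refers to. It rests on other trials having given MK-7 without reported harm, but it states no dose for them, nor does the protocol give the dose of the study it cites there. The doses given for earlier trials (463 μg/day, below 463 μg/day, 200–500 μg/day) all lie below 1000 μg/day as well as far below 1 g/day. As written, no figure in the document supports the assurance at 1 g/day. Correcting a unit would narrow the gap but would not by itself supply a figure at 1000 μg/day either.

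**The case against.** The contradiction itself is hard to contest, so the best case on the other side limits what is built on it.

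- **It may be only a unit slip, with the supplied product fixing the dose in practice.** That is possible. But the gram figure appears three times, including in the Methods, and the protocol gives no capsule strength or count that would act as a safeguard. The document does not show which figure is the slip.
- **The rationale cites a gram-range trial, so 1 g/day is not without precedent.** The citation is real and belongs in the account. However, it is the proposed dose of an ongoing trial with no safety result reported here, so it does not support the safety assurance. It should join the same unit check.
- **The rationale is directional: 463 μg/day was too little, so more is given.** This stands in part. Both figures exceed 463 μg/day, so the direction of the argument survives under either. The size of the step, about 2-fold or about 2,160-fold, does not, and the claim that so high a dose is justified depends on that size.
- **The cited safety study may have used a relevant dose.** Its dose is not stated in the protocol. The fair conclusion is that no supporting figure is shown, not that none exists.
- **No error in the consent, ethics or product documents has been shown.** Correct. They are not available here, and Figure 1 is not shown. This is a reason to check them, not evidence that they are wrong.

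**Conclusion.** The concern holds. The protocol states the active dose as 1000 μg/day once and as 1 g/day three times, exactly 1000-fold apart, and nothing in the readable text resolves it. The safety assurance is attached to the 1 g/day figure, for which the protocol shows no supporting dose data. How large a step the dose rationale is defending also cannot be read until the figure is settled.

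The conclusion rests only on unit conversion and on the wording of the four places. It assumes nothing about which dose is intended. It does not touch the sample size, power or planned analysis, none of which uses the dose. It must be fixed because it leaves the intervention undefined.

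**What to change.** The sponsor should confirm the intended dose and make the Abstract, both statements in the Introduction and the treatment paragraph of the Methods agree, in one unit. Adding the capsule strength and the number of capsules per day would make the pill count interpretable and help prevent a recurrence. The figure should be verified against the supplied product and its label, the ethics-approved documents and the consent text. The 2 g three-times-weekly figure quoted for the other trial should be checked against its source at the same time.

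The safety sentence should then be reread against the confirmed dose and limited to doses that the cited trials actually gave, with those doses stated. Which figure is correct is for the sponsor to establish.

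The cost is a text correction or protocol amendment, plus a check of labels and consent wording. No recalculation or redesign follows.

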Radial artery applanation tonometry with the a high-fidelity, pencil-type SPT-301 (Millar Instruments, Houston, TX) probe interfaced with a computer running Sphygmocor software (ArtCor, Sydney, Australia), will be performed to estimate central hemodynamic indices. The Sphygmocor software regenerates the aortic pulse waveform via mathematical transformation of the radial pulse waveform (generalized transfer function). Aortic pulse waveform will be calibrated by inserting the brachial systolic BP (bSBP) and brachial diastolic BP (bDBP) recorded immediately before the Sphygmocor measurement (25). Augmentation pressure (AP) will be defined as the difference of aortic pressures between the second and first systolic peaks. Augmentation index (AIx) will be calculated as the ratio of AP to aortic pulse pressure (PP) and will be expressed as percentage (%). Heart rate-adjusted AIx (AIx(75)) will be estimated by adjusting AIx at an inverse rate of 4.8% for each 10 beats per minute increase in heart rate (2;6). Aortic PWV will be determined by performing applanation tonometry at the carotid and femoral arteries with the above-described pencil-type tonometer (26). Pulse waveforms will be referenced to a concurrently recorded ECG, and pulse wave transit time between the subsequent recording sites will be calculated using the foot-to-foot time difference between carotid/femoral waveforms (27). Body surface distances from the suprasternal notch to the carotid recording site (distance A) and from the suprasternal notch to the femoral recording site (distance B) will be measured and pulse wave travel distance will be calculated by subtracting the distance B from distance A. Aortic PWV will be estimated by dividing the pulse wave travel distance to transit time. We will measure PWV over ten consecutive heartbeats to cover a complete respiratory cycle. The first valid tonometric measurement will be used in statistical analysis (25).

Secondary outcomes will be the changes in ambulatory BP indices.

*ABPM with the Mobil-O-Graph device*

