Brachial and central aortic BP, AIx and PWV will be recorded under ambulatory conditions over 24 hours with the brachial cuff-based oscillometric device Mobil-O-Graph (IEM, Stolberg, Germany) (28). The BP-detection unit of this device was validated according to the criteria of European Society of Hypertension/European Society of Cardiology (ESH/ESC). The monitor is programmed to measure BP 3 times per hour during daytime (07:00 to 22:59) and 2 times per hour during nighttime (23:00 to 06:59). ABPM will be considered complete when >80% of readings will be valid with ≤2 non-consecutive daytime hours with <2 valid recordings and ≤1 nighttime hour without valid recording. Participants with incomplete or invalid recordings will be asked to repeat ABPM within the next week.

The methodology incorporated by the Mobil-O-Graph device is described in detail elsewhere (29). After the oscillometric recording of brachial BP, the cuff re-inflates at the diastolic phase, acquiring the brachial pressure waveforms for ~10 seconds with a high-fidelity pressure sensor (MPX5050, Freescale, Tempe, AZ, USA). Subsequently, the software (HMS version 4.5) regenerates the aortic pulse waveform by means of an ARCSolver algorithm using a generalized transfer function. The calculation of central aortic pressures was based on the C1 (brachial systolic BP /diastolic BP) calibration method. The Mobil-O-Graph device performs also wave separation analysis by decomposing the aortic pulse waveform into forward- and backward-traveling pulse waves with a triangular aortic flow waveform (27). Utilizing parameters from pulse wave and wave separation analyses, the ARCSolver algorithm estimates the following indices:

1. augmentation pressure, defined as the difference of the pressure at second minus the pressure at first inflection point of the systolic phase of pulse wave;
2. AIx, an index of pulse wave reflection at the level of microcirculation, defined as the ratio of augmentation pressure to aortic PP;
3. PWV, a direct marker of arterial stiffness, calculated from the reconstructed aortic pulse waveform via mathematical algorithms, taking into account the characteristic impedance and age and assuming a three-element Windkessel model.

*Study endpoints*

We will consider two primary endpoints:

-Progression of aortic stiffness, assessed by the absolute change in the value of PWV after 1.5 years of treatment compared to PWV at baseline before the initiation of treatment.

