We performed two separate power calculations for our two separate, primary endpoints. The only published study so far assessing dp-ucMGP and clinical hard end-points in PD patients, showed that after a median follow-up of 31 months, a significantly higher incidence of fatal/non-fatal CV events occurred in the patients with high dp-ucMGP levels (64.6% versus 39%). Until to-date no RCTs have been conducted in PD patients, therefore our calculation will be based on already published data in similar populations. We consider that a 28% difference in the incidence of CV events among arms is a significant treatment effect and we expect that the incidence of CV events would be 56% in the placebo and 28% in the treatment group, during the 18 month follow-up. Therefore, with a two-sided significance level of 5%, t-test and 80% power, 96 participants will be required. Accounting for a drop-out of 20%, we will enroll 120 patients (60 in each arm).

For the primary outcome of arterial stiffness progression we performed a separate power analysis. Based on previous studies, we expect that the increase in PWV value (absolute difference from baseline to the end of the study) will be 3 m/s after 1.5 year at the placebo group with an assumed standard deviation of 0.90 m/s (3, 30, 31) and we consider that an absolute difference of 20% in PWV increase among groups, is a significant treatment effect (32, 33). Accounting for an estimating drop-out rate of 20%, with a two-sided significance level of 5%, t-test and 80% power, 120 patients will be required (60 in each group) to detect a significant treatment difference.

*Monitoring*

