During the study period, 6 follow-up visits will take place, at months 3, 6, 9, 12, 15 and 18 respectively. In all these visits, patients will be interviewed regarding the compliance and potential side effects (and pills will be counted), and clinical examination and routine blood sampling will be performed. To evaluate the patients’ compliance, the drug boxes will be thoroughly checked and remaining pills will be counted and reported. As before enrollment, all patients will undergo standard, regular follow-up visits every month in their PD unit. At the end of the follow-up period, all plasma and serum parameters that were measured at baseline, along with PWV will be re-assessed. The occurrence of the trial’s endpoints will be documented by death certificates, medical files and records and integrated interview at the last visit or telephone interviews. During the study period, all potential adverse events will be closely monitored and recorded. These data will be evaluated thoroughly. The criteria for early termination of the trial will be withdraw of the written consent, death, kidney transplantation, severe allergic response to MK-7 and medical necessity for treatment initiation with vitamin K antagonists.

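### The primary PWV change is one tonometric acquisition minus another; averaging two per visit would recover some precision at little cost

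*Protocol*

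**What the plan says.** In Materials and Methods, the section on tonometric measurement with the Sphygmocor device describes one carotid-femoral acquisition: "We will measure PWV over ten consecutive heartbeats to cover a complete respiratory cycle". It then fixes which value is analysed: "The first valid tonometric measurement will be used in statistical analysis".

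Study endpoints defines the first primary endpoint as progression of aortic stiffness, "assessed by the absolute change in the value of PWV after 1.5 years of treatment compared to PWV at baseline". Under Monitoring, the visits at months 3 to 15 cover compliance, side effects, clinical examination and routine bloods. Only at the end of follow-up are the baseline laboratory parameters, "along with PWV will be re-assessed".

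Sample size calculation assumes that the PWV increase "will be 3 m/s after 1.5 year at the placebo group with an assumed standard deviation of 0.90 m/s", and takes "an absolute difference of 20% in PWV increase among groups" as the effect to detect.

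The Protocol nowhere plans a duplicate tonometric acquisition or an average of acquisitions, and it gives no figure for the error of a single reading.

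**The concern.** A change score built from one acquisition at each of two visits contains the error of a single acquisition twice. Ten heartbeats within one acquisition average out beat-to-beat and respiratory variation. They do not average out error that is fixed for that acquisition, such as where the hand-held probe sits on the carotid and femoral arteries. Only a repeat acquisition with the probe re-positioned can reduce that part.

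What is at stake is the width of the confidence interval for the treatment difference in a primary endpoint. Enrolment is set at 120 patients in three centres and no interim PWV is listed, so the precision of the two measurements is one of the few inexpensive ways to narrow that interval.

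**Working it through.** **Inputs from the Protocol (Sample size calculation).** Placebo increase 3 m/s; SD of the change 0.90 m/s; 20% effect, read as 0.20 × 3 = 0.6 m/s; two-sided 5%; t-test; 80% power; 20% dropout; 60 per arm, hence 60 × 0.8 = 48 completers per arm.

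**The plan's own figure.** The standardised effect is 0.6/0.90 = 0.667. A t-test at 80% power needs 37 per arm, and 74/0.8 = 92.5, so 93 patients. The normal approximation gives 36 per arm, and 72/0.8 = 90. The stated 120 therefore does not follow from 80% power. It matches 90% power by the normal approximation (48 per arm, 96/0.8 = 120). With 48 completers per arm, t-test power is 0.898. The standard error of the treatment difference is 0.90 × √(2/48) = 0.18 m/s.

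**Variance of the change.** Let s be the SD of the error of one reading.

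- One reading per visit: Var(change) = Var(true change) + 2s².
- Mean of two readings with independent errors at both visits: Var(change) = Var(true change) + s². The variance falls by s².
- If half the error variance is shared by both readings of a visit, only the other half is averaged, and the variance falls by s²/2.

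**Assumptions.** The Protocol does not give s, so 0.3 to 0.5 m/s is assumed. The 0.90 m/s is taken to describe a change between single readings, so the starting variance is 0.90² = 0.81.

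| s (m/s) | 2s² as share of 0.81 | SD, independent errors | Interval narrower by | Worth, in extra patients | Power, 48 per arm |
|---|---|---|---|---|---|
| 0.3 | 22% | √(0.81 − 0.09) = 0.849 | 6% | 0.81/0.72 = 1.125, 12% | 0.929 |
| 0.4 | 40% | √(0.81 − 0.16) = 0.806 | 10% | 0.81/0.65 = 1.25, 25% | 0.950 |
| 0.5 | 62% | √(0.81 − 0.25) = 0.748 | 17% | 0.81/0.56 = 1.45, 45% | 0.973 |

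| s (m/s) | SD, half the error variance shared | Interval narrower by | Worth, in extra patients | Power, 48 per arm |
|---|---|---|---|---|
| 0.3 | √(0.81 − 0.045) = 0.875 | 3% | 0.81/0.765 = 1.06, 6% | 0.914 |
| 0.4 | √(0.81 − 0.08) = 0.854 | 5% | 0.81/0.73 = 1.11, 11% | 0.926 |
| 0.5 | √(0.81 − 0.125) = 0.828 | 8% | 0.81/0.685 = 1.18, 18% | 0.940 |

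**If 0.90 m/s came from averaged readings instead.** The single-reading SD would then be √(0.81 + 0.09) = 0.95 to √(0.81 + 0.25) = 1.03 m/s with independent errors. Power falls to 80% only at an SD of 1.04 m/s, so the stated target would still be met.

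**If the assumed progression is too high (illustration only).** With a placebo increase of 2 m/s, a 20% effect is 0.4 m/s. At SD 0.90 and 48 per arm, power is 0.58 with single readings. It is 0.63–0.74 with averaged readings if errors are independent, and 0.60–0.65 if half the error variance is shared.

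**The case against.** The strongest reply is that this is a deliberate choice and not an error. The rule is stated in advance and cites a source, only valid readings count, and each reading already spans ten heartbeats. Taking the first valid reading also leaves nobody free to choose among readings, which has value in a trial that calls itself open-label. All of that stands. But a mean of two readings fixed in advance leaves no more room for choice.

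The reply also holds that the gain is of unknown size and unnecessary. This is partly right. The size rests on an assumed error, and the independent-error figures are a best case: error from the patient's state that day, or from a surface distance measured only once, is common to both readings and does not average out. On the plan's inputs the PWV comparison already has about 90% power. If 0.90 m/s describes single readings, their error is already in the sample size.

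Three stronger readings might be inferred, and the documents support none of them.

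- *The first reading is distorted because the patient has not yet settled.* The Protocol gives no rest conditions and no data on this. A consistent shift of that kind would occur at both visits and in both arms, with PWV assessors blinded, and would largely cancel in the comparison of changes.
- *The planned 0.6 m/s is small beside single-reading error.* It exceeds every value in the assumed range of 0.3 to 0.5 m/s. The relevant yardstick for a group difference is its standard error of 0.18 m/s, and 0.6 is more than three times that.
- *Later valid readings are taken and thrown away.* The Protocol does not say that any are taken.

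**Conclusion.** The point holds as an avoidable loss of precision in a primary endpoint. It is neither a bias nor a shortfall of power on the plan's own assumptions. The direction of the gain is certain wherever some reading error is independent between acquisitions. Its size is not known from the documents. For an assumed error of 0.3 to 0.5 m/s per reading, intervals would be 6–17% narrower at best, and about 3–8% narrower if half the error variance is shared within a visit. Both ranges take 0.90 m/s as the SD of a single-reading change. The gain would count for more if the 3 m/s progression proves too high. The change is worth making because it is cheap, not because the primary analysis fails without it.

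**What to change.** Replace the sentence on the analysed reading with a rule such as: at baseline and at month 18, two valid carotid-femoral PWV acquisitions are taken at the same sitting, with the probe re-positioned between them, and their mean is analysed; if only one is valid, that one is used. The last clause means that the rule creates no additional missing data. If a third acquisition is wanted when the first two disagree, fix the numerical threshold and the way the three are combined in advance; otherwise leave it out.

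The cost is a few extra minutes with the same device and operator at two assessments that already take place. The Protocol does not cost this, so that is a judgement. The sample size need not change.
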